### 4.3 Exclusion criteria

A potential subject who meets any of the following criteria will be excluded from participation in this study:

- Use of oral anticoagulation drugs; patients may be included when they have been switched to LMWH
- Patients on vitamin K antagonists with a supra-therapeutic anticoagulation at admission who require vitamin K supplementation to correct this, or were administered vitamin K for this reason within the preceding 5 days
- Patients already using vitamin K supplements at admission
- Participation in another intervention study
- Direct admission to an intensive care unit (ICU) for invasive ventilation at presentation
- Confirmed active pulmonary embolism or deep venous thrombosis prior to inclusion
- Known allergy to any of the components of the study medication or placebo
- Patients who are hemodialysis dependent at admission
- Pregnancy at the time of inclusion

- Diagnosed malignancy at the time of inclusion

#### 4.4 Sample size calculation

This is the first study evaluating the effects of oral vitamin K in COVID-19 patients. In accordance with standards for early phase clinical trials the primary outcomes of this study were chosen to facilitate a study with a relatively small sample size.

The key primary outcome will be the effect of vitamin K supplementation on elastic fiber degradation, determined by measuring plasma desmosine (pDES) in the intervention versus the control group. In the previous study of 135 COVID-19 patients pDES has a log-normal distribution, with a mean of  $\ln$  of 5.99 with a standard deviation of 0.603. The effects of vitamin K2 on this outcome have never been studied, however, we consider a difference in  $\ln(\text{pDES})$  of 10% to be clinically significant. An independent samples t-test (with  $\alpha=0.05$  and  $\beta=0.20$ ) would be statistically significant between two groups of 16 persons (total study population 32 persons).

Based on these two outcomes the sample size of 40 persons allows for a 10% loss to follow-up for the per-protocol analysis.

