### Secondary objectives:

- To evaluate the effects of oral vitamin K2 supplementation on adverse events and disease progression during COVID-19 requiring hospital admission
- To evaluate the effects of oral vitamin K2 supplementation on hepatic vitamin K status, as measured by circulating PIVKA-II, during COVID-19 requiring hospital admission

Exploratory objectives:

- To evaluate the effect of vitamin K2 supplementation on circulating (undercarboxylated) protein S
- To evaluate the effect of oral vitamin K2 supplementation on respiratory failure requiring intubation and mechanical ventilation or leading to death
- To evaluate the effects of supplementation of oral vitamin K2 on disease severity on lung CT scan
- To evaluate the effect of oral vitamin K2 supplementation on active MGP concentrations
- To evaluate the effect of oral vitamin K2 supplementation on TFPI and normative APC sensitivity ratio and prothrombin (Echis Carinato test)
- To evaluate the effect of oral vitamin K2 on circulating MMP9
- To evaluate the effect of oral vitamin K2 on systemic inflammation by measuring cytokines and inflammatory mediators like interleukin-6 (IL-6)
- To further explore the pathophysiology and biomarkers for COVID-19 susceptibility, severity and disease progression, including Vitamin K epoxide reductase complex subunit 1 (VKORC-1) gene polymorphism

**Study design:** This is a phase 2a, double-blind randomized placebo-controlled intervention trial (1:1 randomization).

**Study population:** A total of 40 patients with respiratory failure due to (proven) COVID-19 disease who are admitted to the Canisius Wilhelmina Ziekenhuis (CWZ) in Nijmegen, the Netherlands will be enrolled.

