### **10.2 Secondary and exploratory study parameters**

Adverse events will be compared by tabulating all grade 3 and 4 adverse events for each patient and calculating the proportion of in each group. The incidence of complications will be compared between groups with the chi-square test or Fishers exact test.

In the exploratory analyses, we will assess differences by comparing mean values between the groups using either a two-tailed student's t-test or non-parametric equivalents, paired if pre-treatment values are compared with post-treatment values, unpaired if comparisons are made between groups. For discrete variables (e.g. the number of positive assays), the chi-squared test or Fisher's exact test will be used (two-tailed).

As an exploratory analysis data will also be visualized on an individual patient level to evaluate the progression or correction of vitamin K deficiency in relationship to other parameters associated with COVID-19 disease severity.

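### Protocol section 4.4 defines the clinically significant difference as 10% of a mean logarithm, which amounts to an unstated and unjustified 45% fall in desmosine

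*Protocol*

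**What the plan says.** Section 4.4 of the protocol names desmosine as the key primary outcome, "determined by measuring plasma desmosine (pDES) in the intervention versus the control group". From an earlier cohort of 135 COVID-19 patients it takes a log-normal distribution with a mean of ln(pDES) "of 5.99 with a standard deviation of 0.603". It notes that the effect of vitamin K2 on desmosine has never been studied and regards a difference in ln(pDES) "of 10% to be clinically significant". With alpha 0.05 and beta 0.20, an independent samples t-test "would be statistically significant between two groups of 16 persons (total study population 32 persons").

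The section closes: "Based on these two outcomes the sample size of 40 persons allows for a 10% loss to follow-up for the per-protocol analysis". No second calculation is shown.

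Section 10.1 plans an independent samples t-test on log-transformed desmosine. ANCOVA is allowed as an addition but not required. The Summary gives "1:1 randomization".

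**The concern.** A difference between two means of logarithms is the logarithm of a ratio. It needs no further percentage: 0.105 ln units is a 10% fall, whatever the mean. Taking 10% of the mean logarithm gives a quantity that depends on where the log scale has its zero, and so on the unit in which desmosine is reported. It cannot serve as a threshold of clinical relevance unless it is translated back to desmosine, and the protocol never does this.

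What is at stake is how the key primary result is understood. The only figure that section 4.4 offers for the effect is 10%, while the effect that the sample size supports is several times larger on the scale that clinicians and ethics reviewers would use. The protocol also gives an expected average stay of 6 days (section 3), so the plausibility of a large change in that time deserves an explicit statement.

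**Working it through.** **Inputs (section 4.4 unless noted).** Mean of ln(pDES) 5.99, SD 0.603, alpha 0.05, power 0.80, 1:1 allocation (Summary). Section 4.4 does not state sidedness; two-sided is assumed. Section 10.2 gives two-tailed tests only for the exploratory comparisons.

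**1. Reproducing 16 per group.** Read 10% as a share of the mean logarithm:

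- δ = 0.10 × 5.99 = 0.599 ln units
- standardised effect = 0.599 / 0.603 = 0.993
- normal approximation: n = 2 × (1.960 + 0.842)² / 0.993² = 15.9, so 16 per group

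The exact (noncentral t) calculation gives 16.9, so 17 per group; power at 16 is 77.6%. A one-sided test would need 13 (normal approximation) or 14 (exact).

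Other readings of 10% do not come near 16:

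| Reading of 10% | δ (ln units) | n per group |
|---|---|---|
| 10% of the mean logarithm | 0.599 | 16 |
| 10% fall in desmosine, −ln(0.9) | 0.105 | 515 |
| 0.10 ln units | 0.100 | 571 |
| 10% rise in desmosine, ln(1.1) | 0.095 | 629 |

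The protocol's own numbers therefore identify the reading.

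**2. What 0.599 ln units means for desmosine.**

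- geometric mean: exp(5.99) = 399
- after the fall: exp(5.99 − 0.599) = 219
- ratio: exp(−0.599) = 0.549, a 45% fall (in the other direction, exp(0.599) = 1.82, an 82% rise)

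**3. Dependence on the unit.** Express the same data in a unit 1000 times larger, so that every value is divided by 1000. The SD of the logarithm stays at 0.603, but its mean becomes 5.99 − ln(1000) = −0.92. Ten percent of that is 0.092 in size, and the same recipe asks for about 679 per group. In a unit 1000 times smaller the log mean is 12.90, and 10% of it, 1.29, is a 72% fall.

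**4. Power for changes in desmosine itself.** Exact two-sided t-test, SD 0.603, 20 per arm:

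| True fall | δ (ln units) | Power |
|---|---|---|
| 10% | 0.105 | 8% |
| 20% | 0.223 | 21% |
| 30% | 0.357 | 45% |

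The fall at which power reaches 80%, and the power for δ = 0.599:

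| Evaluable per arm | Fall at 80% power | Power for ratio 0.55 |
|---|---|---|
| 16 | 46% | 77.6% |
| 18 | 44% | 82.5% |
| 20 | 42% | 86.5% |

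**5. Effect of ANCOVA.** Adjusting for baseline multiplies the SD by √(1 − r²). The correlation r is not given in the protocol. For assumed values of 0.5 to 0.8, the fall at 80% power with 20 per arm is about 38% to 28%, and power for a 10% fall is about 10% to 15%.

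**6. Loss allowance.** 1 − 32/40 = 20%. A 10% loss from 40 leaves 36. Inflating 32 for 10% loss gives 32/0.9 = 35.6, so 36. Starting from the exact requirement of 34, 34/0.9 = 37.8, so 38.

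**The case against.** The strongest defence is that the sentence is literally about ln(pDES), and on that wording 16 per group follows. This stands. A reader might infer an arithmetic slip, or that the authors believed they were powering for a 10% change in desmosine. The protocol does not say so, and the first inference is wrong apart from the choice between 16 and 17. The weakness is in how the effect is defined and in the absence of any translation or justification.

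A reader might also infer that the trial can detect nothing short of a near-halving. That confuses the effect with 80% power and the effect that can be found at all. With 20 per arm, an observed fall of about 32% (2.024 × 0.603 × √(2/20) = 0.386 ln units) would already reach p < 0.05, and a true 40% fall has about 74% power. ANCOVA, where used, improves this further. None of it brings a 10% fall within reach.

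On losses, it is fair to say that 40 does cover a 10% loss against 32, with patients to spare, so the mismatch costs no power. A second calculation, perhaps for dp-ucMGP, may have required 36, which fits 40 with 10% loss exactly. That cannot be checked from the protocol. The point remains a minor correction and is not evidence that the trial is short of patients.

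Finally, a small early-phase study is a legitimate choice, and section 4.4 says that the outcomes were chosen to permit one. That supports keeping 40 patients. It does not support leaving the effect undefined on the desmosine scale.

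**Conclusion.** The point holds in this form: the clinically significant difference in section 4.4 is 0.599 ln units, a unit-dependent quantity equal to a ratio of geometric means of 0.55, or a 45% fall in desmosine, which the protocol neither states nor justifies. For a true 10% fall, power with 20 per arm is about 8%, and about 515 per arm would be needed for 80%.

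These figures rest on the protocol's SD of 0.603, a two-sided test at 0.05 (assumed) and the unadjusted t-test of section 10.1. Over the assumed range of baseline correlations, ANCOVA lowers the fall at 80% power from about 42% to between 38% and 28% with 20 per arm, which does not change the conclusion.

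The use of 16 rather than 17 per group, the 10% loss figure and the reference to two outcomes are minor.

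**What to change.** Keep 40 patients and rewrite the effect statement in section 4.4 on the desmosine scale. Possible text:

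*With an SD of 0.603 for ln(pDES) and a two-sided t-test at 0.05, 18 evaluable patients per arm give about 82% power for a ratio of geometric means of 0.55 (45% lower pDES). Power for smaller effects is lower. The trial is not designed to detect or exclude a 10% change in desmosine.*

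Add a sentence on why a fall of that size is considered relevant and plausible, or say openly that the number was set by feasibility.

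In the same edit:

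- give 17 per group as the exact t-test requirement for 0.599 ln units, or state that 16 is a normal approximation;
- correct the loss allowance: 40 enrolled against 32 evaluable is 20%, and a 10% loss leaves 36;
- show the second calculation (presumably dp-ucMGP) or remove the reference to two outcomes;
- state the sidedness of the test.

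The cost is protocol wording only. No patients, visits or tests are added; the stated sensitivity of the trial becomes less favourable but accurate.

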## **5. TREATMENT OF SUBJECTS**

### **5.1 Investigational product**

Patients will take three tablets of either vitamin K2 menaquinone-7 (333mcg) or placebo per day. Patients taking vitamin K2 MK-7 will receive the total of 999mcg per day from day 1 until day 14 or discharge, whichever occurs earlier.

While concomitant use of oral anticoagulant drugs is an exclusion criteria, all subjects will be treated with prophylactic heparin-based (heparin or any low-molecular weight heparin) anticoagulants according to local hospital protocols.

### **5.2 Escape medication**

If patients develop thromboembolic complications or have another indication for anticoagulant treatment (such as atrial fibrillation) they can be treated with therapeutic dosages of heparin-based (heparin or any low-molecular weight heparin) anticoagulants without being excluded from the study.

## 6. INVESTIGATIONAL PRODUCT

### 6.1 Name and description of investigational product(s)

Investigational product: Vitamin K2, in the form of menaquinone-7 (MK-7), 'Vitamin K2 MK-7' or placebo containing only inactive ingredients.

#### *Structure and function*

Vitamin K represents a family of fat-soluble vitamins with the common chemical structure of 3-substituted 2-methyl-1,4-naphthoquinone. It is found naturally in food as phyloquinone (vitamin K1) and menaquinones (vitamin K2). Phyloquinone is the primary form of vitamin K found in typical Dutch diets: it is found in dark green leafy vegetables (e.g. spinach, lettuce and other salad plants). Menaquinones are a group of compounds with an unsaturated sidechain from 4 to 13 isoprenyl units (vitamin K2 or MK-n). They are found mainly in animal products such as meat, cheese and eggs, and in a fermented soybeans called 'natto'. The vitamin K2 series is synthesized by various Gram-positive bacteria present in the jejunum and ileum [27].

Vitamin K acts as a cofactor for the reaction in which the enzyme  $\gamma$ -glutamyl carboxylase (GGCX) catalyses the carboxylation of glutamic acid (Glu) residues into  $\gamma$ -carboxyglutamic acid (Gla) residues in vitamin K-dependent proteins (Gla-proteins), which is required for their activity. These Gla-proteins are involved in many physiological processes, including blood coagulation and anticoagulation, elastic fiber metabolism and bone mineralisation. MK-7 may have a greater bioactivity than phyloquinone and other menaquinones [27].

#### *Reference values and toxicity*

In a recent publication the European Food Safety Authority noted that there was insufficient data to provide guidance on Daily Reference Values for vitamin K intake. However, they also note that there are no studies that show adverse effects associated with supplementation [27].

#### *Investigational product*

Kappa Biosciences AS (Norway) manufactures a synthetic form of Vitamin K2 MK-7 (a.k.a.: K2VITAL®). Vitamin K2 MK-7 is manufactured by Kappa Biosciences AS in Norway as a pure crystalline powder. Since the amount of the active ingredient per tablet is so low, it is shipped to BASF AS (Denmark) for preparation of a formulation suitable for manufacturing of tablets. This is a microencapsulated Vitamin K2 MK-7 product with inactive ingredients (see documents in Section D). The active, microencapsulated product is further shipped to Optipharma (Norway) who manufacture tablets containing 333 µg Vitamin K2 MK-7 and placebo tablets. Finished tablets will be packed by Optipharma and labelled by Kappa Bioscience AS.

Vitamin K2 is registered for use as ingredient in food supplements in the Netherlands and has also been approved by the European Food Safety Authority (EFSA). The manufacturer will assess the uniformity and stability of the finished product.

## 6.2 Summary of findings from non-clinical studies

The only well-described function of vitamin K is to serve as a cofactor for the enzyme  $\gamma$ -glutamate carboxylase (GGCX) during the posttranslational carboxylation of glutamate residues into  $\gamma$ -carboxyglutamate (Gla) [28]. Proteins undergoing this carboxylation are known as Gla-proteins. Currently 17 Gla-proteins have been identified, and in all cases in which their function is known, the carboxylation step is a prerequisite for their biological activity [29].

After its initial discovery in liver, GGCX was found to be present in almost all mammalian tissues including lung, heart, kidney, spleen, testis, cartilage and bone [30]. It was also identified in skin, both in the dermis and in the epidermis [31]. Most Gla-proteins are expressed in only one type of tissue, such as the procoagulant factors II, VII, IX and X which are all synthesized in the liver, and osteocalcin, which is uniquely synthesized in bone [32]. MGP, on the other hand, has a much wider expression pattern and was identified in most extrahepatic tissues in which also GGCX was found [6]. Different functions have been reported for the various Gla-proteins: the most well-known are those involved in hemostasis, such as prothrombin and the clotting factors VII, IX and X [32].

Another family of Gla-proteins is that of the calcification inhibitors: osteocalcin, MGP and Gla-rich Protein (GRP, also known as UCMA) [33]. MGP is a strong inhibitor of soft tissue calcification and was also found to be associated with the elastic fibers, for instance in the dermis [34] and in the large arteries [4], where it is synthesized by fibroblasts [35] and vascular smooth muscle cells [36], respectively. As was demonstrated by Price, small calcification inhibitors like osteocalcin and MGP are essential in the prevention of elastin and collagen fibril calcification, a principle that was designated as mineralization by inhibitor exclusion [37]. Poor vitamin K status has been demonstrated to be associated with vascular stiffening [38] and excessive calcium salt precipitation, both in animal models [39] and in humans [40]. It is to be expected that a similar mechanism is operational in the elastin fibrils in the lung.

Toxicity studies were conducted in mice, chicks and rats. Vitamin K1 in single oral doses up to 25,000 mg/kg BW, produced no fatalities in mice. Daily doses as high as 2000 mg/kg body weight vitamin K1 produced no ill effects [41]. In an acute oral toxicity test, mice were given a single oral dose of 2000 mg/kg body weight Vitamin K2 MK-7 (limit dose) where no toxicities were observed during the 14-day observation period. In a subchronic oral toxicity test in rats, animals were administered Vitamin K2 MK-7 for 90 days by gavage at the following doses: 0 (vehicle control, corn oil), 2.5, 5, and 10 mg/kg body weight per day. The no observed adverse effect level (NOAEL) of MK-7, when administered orally to rats for 90 days, was considered to be equal to 10 mg/kg body weight per day, the highest dose tested, based on lack of toxicity [42, 43].

### 6.3 Summary of findings from clinical studies

A Japanese dish called 'natto' that consists of fermented soy beans and is extremely rich in vitamin K2 has been eaten for nearly 1000 years. It has been postulated that this may be the reason for the low incidence of osteoporosis in these areas [25]. Several studies have been conducted in healthy volunteers consuming natto daily. The amount of natto consumed by participants varies between studies often contained up to 900µg vitamin K2 per day without any adverse effects [44-47]. These studies demonstrated a rapid increase in serum MK-7 after ingestion, figure 5 [48].

[figure not shown]

**Figure 5:** Plasma concentrations of vitamin isoforms (phylloquinone, menaquinone-4 and menaquinone-7) in n=5 subjects before and up to 4 days after eating one package of natto (50 grams) [48].

Furthermore, in studies where the ingested natto had an equivalent of around 900µg Vitamin K2 MK-7 per day a rapid increase both in plasma levels of MK-7 and an increase in carboxylated osteocalcin (a vitamin K dependent bone protein) were seen as early as 1 day after ingestion, figure 6 panel A and B [47]. This effect already appears to be near its maximum on day 7 after starting, with only a small not statistically significant increase, between day 7 and day 14, figure 6 panel C and D [46].

[figure not shown]

**Figure 6:** Panel A and B: N=8 healthy adults ingested 50 grams of natto containing 775µg/100g, 1289µg/100g or 1765µg/100g vitamin K2 MK-7 once a day for 7 days. Serum MK-7 and γ-carboxylated osteocalcin (osteocalcin activated by vitamin K) were measured at baseline and after 1 and 7 days [46]. Panel C and D: N=16 healthy adults ingested 50 grams of natto containing 865µg/100g, 1295µg/100g or 1765µg/100g vitamin K2 MK-7 once a day for 14 days. Serum MK-7 and γ-carboxylated osteocalcin (osteocalcin activated by vitamin K) were measured at baseline and after 7, 10 and 14 days [47].

Many clinical trials have been conducted using vitamin K2, recently reviewed in [25]. These studies consistently show that vitamin K2 administration reduces the levels of uncarboxylated vitamin-K-dependent proteins, including dp-ucMGP, PIVKA-II and ucOC.

A number of trials, and available systematic reviews, have demonstrated significant effect of vitamin K2 in reducing osteoporotic fractures in postmenopausal women. Despite dosages as high as 45mg vitamin K2 (in the form of menaquinone-4) per day, these trials have not reported adverse events, including thrombotic or bleeding events [49].

Vitamin K deficiency has been well established in hemodialysis patients and has been implicated as the link between fractures and vascular calcification in these populations. As such, several trials have been conducted looking at vitamin K2 supplementation in these

populations. In a recent study hemodialysis patients were supplemented with 2000µg Vitamin K2 MK-7 three times a week for 18 months without any adverse effects [50].

Given its potential role in reversing vascular calcification, many studies have investigated whether it can prevent cardiovascular disease. These trials have generally been conducted in small study groups and therefore occasionally report contradictory results. A currently ongoing trial 400 men between 65-74 years old are receiving either 720µg vitamin K2 MK-7 per day or placebo [51]. Though data from this trial is not yet available, there have been no major safety issues ([name], personal communication).

To date there is no data on vitamin K supplementation during infectious diseases, with the exception of instances when it is given to correct bleeding disorders resulting from PT elongation, such as during Ebola virus disease [52].

#### **6.4 Summary of known and potential risks and benefits**

The European Food Safety Association reviewed guidelines for vitamin K intake in 2017. Given the paucity of information no tolerable upper intake level was set for vitamin K by the Scientific Committee on Food (SCF) [27]. Their review of the available literature did not find any adverse events thought to be associated with vitamin K toxicity at any studied dose in persons not using VKAs. Animal investigations have found no adverse effect after daily vitamin K administration of 2,000 mg/kg body weight for 30 days. Newborns are routinely administered supraphysiological doses of vitamin K parenterally (ranging from 0.2 mg/kg body weight to a 1 mg bolus dose), which have been demonstrated to induce mean/median serum vitamin K concentrations in the first week of life up to 1,000-fold higher than non-fasting adult 'normal' values. Furthermore, studies investigating different doses of parenteral vitamin K prophylaxis in infants looked the production of vitamin K metabolites, vitamin K recycling and vitamin K catabolic pathways and found that they were capable of metabolising large vitamin K doses [27].

Though these studies have generally been performed using vitamin K1, there is no evidence for toxicity of vitamin K2 MK-7 at dosages of 900µg/day or 2000µg 3 times per week, see section 6.3.

Given the poor appetite generally seen in COVID-19 patients and the fact that nutritional supplementation in Dutch hospitals does not contain significant amounts of vitamin K, there is little risk of patients inadvertently receiving higher dosages of vitamin K than intended.

